#### First session

The experience of having a severe illness sets in motion a variety of existential thoughts about life and death and about what is important in life. Thus, the first session seeks to clarify which values the patient has and which actions bring him/her into alignment with these values. It also reveals which difficulties prevent him from acting the way he really wants to act and how a given behaviour is related to what is important to him. For example, a heart patient may have a value linked to health and the associated behaviour might be to follow the dietician’s advice and to continue exercising. His difficulties might be associated with fear of having another heart attack, which could lead to inactivity. The assigned homework in this session is completing a matrix (see Fig. 2) [31].

**Fig. 2 Fig2:**
[figure not shown]
The matrix shows the significance of discovering one’s values to overcome difficulties

#### Second session

After a heart attack, patients commonly fear another attack. The second session is thus based on anxiety. Initially, it is emphasized that anxiety is a normal feeling and a natural reaction to danger. Anxiety becomes inconvenient when connected to an “imagined” danger and/or takes on the character of an “excessive” danger. The physiology of anxiety is thoroughly reviewed, so that the patient will be able to recognize its physical components and thus distinguish between a regular heart attack and anxiety symptoms. When the basic conditions are explained in this way, the anxiety circle is reviewed; the anxiety circle describes how an experienced threat can cause physical reactions and catastrophizing thoughts. This often leads to avoidance behaviour and/or safety behaviour. Of course, when anxiety-filled situations are avoided, anxiety diminishes, but the expectation of anxiety rises, and the person may begin to fear a similar situation in the future (see Fig. 3). This session ends with the introduction of various types of strategies as well as explanations of why it is important gradually to expose oneself to situations in which it is difficult to keep anxiety at a low level. The homework for this session is to begin gradual exposure and to apply the strategies in everyday life [32].

#### Third session

After CAD and surgically treated VHD, several lifestyle changes are recommended, such as a change of diet and initial part-time sick leave. It can be difficult to change lifestyle and incorporate new habits. Therefore, the third session deals with the analysis and consequences of current behaviour. For example, a patient is satisfied with his work, wherefore he works 50 h per week. The consequence of this is that in the short term he is satisfied and happy while not having time to recover from his illness, which can have serious implications in the longer term. Homework in this session is the completion of a “behavioural analysis” form (see Fig. 4).

**Fig. 4 Fig4:**
[figure not shown]
Behavioural analysis demonstrates the consequences of behaviour and what leads to the behaviour

#### Fourth session

CAD and VHD give rise to many concerns that potentially limit the patient. Worry is a way of thinking that can lead to problem-solving, but it can also lead to pondering. Therefore, the fourth session is about recognizing one’s own thinking and the influence it has on one’s behaviour in order to move towards a more constructive behaviour. The session broadly explains several strategies including acceptance and diffusion (creating distance to thought). Homework is to recognize if/when one ponders/worries and if so, to possibly apply some of the strategies [33].

#### Fifth session

The last session focuses on how to make optimal use of the strengths the patient possesses. It illustrates how to balance demands and strengths with an emphasis on committing to nourishing and long-term strategies. It can for example be helpful to apply new strategies such as breaking up a larger task into smaller steps. In the latter half of this session, the matrix from the first session is explained and included more explicitly to examine whether the participants may have changed their strategies and comprehension in comparison with the beginning of the course. The session is concluded with feedback on the entire process [34, 35].

### Primary outcome

The primary outcome is mean (method of aggregation) change (metric) in psychological distress (domain) measured by HADS total score (specific measurement) from baseline to three months (time) in the intervention group compared with the usual care group. This outcome may be subject to ascertainment bias when blinding is not possible, e.g. social desirability bias causing participants to respond more favourably. We have attempted to limit this by administering the paper questionnaires to be filled in unsupervised. Furthermore, since both the intervention and the control group receive usual CR in the same cardiac settings, both groups may be subject to similar social desirability bias. At the 6-month follow-up, we anticipate that this bias will be reduced.

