### CBT intervention

The CBT intervention is a psycho-educational group course conducted as five sessions led by an experienced nurse under the supervision of a psychologist who is a specialist in CBT. There will be 3–4 patients in each group for the therapy sessions. Each session will last 2 h and has a set structure, with the use of homework and always ending with the opportunity to give feedback [28].

The five sessions contain:
Introduction to CBT and mapping of own valuesAnxiety and anxiety reduction techniquesFunctional analysis (awareness of consequences of own behaviour)Concerns and strategies for dealing with concernsBalance between requirements and forces as well as conclusion

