### Secondary outcomes

Secondary outcomes are adherence to CR defined as > 80% participation in planned training sessions (used as a secondary outcome under the hypothesis that participation in group-based therapy will improve CR adherence), health-related QoL measured by the questionnaire HeartQoL, return to work, marital status, adherence to medication and lifestyle interventions for CVD risk factor goals defined as four separate outcomes: HbA1c < 48, BP < 135/85 mmHg, BMI < 30 and LDL < 1.4 mmol/l, physical activity (days per week with ≥ 30 min of moderate physical activity) and cardiovascular readmissions at 12 months.

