### Data management

Data will be collected at baseline and follow-up visits. Questionnaire responses (all on paper) will be entered into electronic form in REDCap immediately after the assessment. Data from patient records (all electronic) will also be entered into REDCap. All participants will be identified by unique study identification numbers that will be included in a password-protected file. Data will be stored in accordance with the rules of the Danish Data Protection Agency. REDCap meets all criteria for the handling of patient data in accordance with the laws on the processing of personal data. The principal investigator [name] will have unlimited access to the final trial dataset.

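### The plan expects less reporting bias in HADS at 6 months but specifies no between-arm comparison there, and the shared-rehabilitation argument does not cover the therapy given to one arm only

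*Protocol article*

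**What the plan says.** All references are to the protocol article.

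- **Primary outcome.** The endpoint is mean change "measured by HADS total score (specific measurement) from baseline to three months (time) in the intervention group compared with the usual care group". The section concedes that "This outcome may be subject to ascertainment bias when blinding is not possible, e.g. social desirability bias causing participants to respond more favourably". It then gives three answers. The first is a procedure: "We have attempted to limit this by administering the paper questionnaires to be filled in unsupervised". The second is an argument from the usual CR that both arms receive in the same setting, and the third is an expectation that the bias will be smaller at 6 months: "both groups may be subject to similar social desirability bias. At the 6-month follow-up, we anticipate that this bias will be reduced".
- **Schedule (Table 1).** HADS is collected at baseline, 3 months and 6 months.
- **Secondary outcomes.** The list opens with "Secondary outcomes are adherence to CR defined as > 80% participation in planned training sessions" and goes on to quality of life, return to work, four risk-factor thresholds, physical activity, readmissions and others. It contains no HADS outcome at any time point.
- **Statistical analysis.** The primary model takes the 3-month score as the response and enters both the baseline and the 6-month score as adjustment variables.
- **Intervention and CBT intervention.** Only the intervention arm receives the five sessions, in groups of 3 to 4 led by a nurse. On their format: "Each session will last 2 h and has a set structure, with the use of homework and always ending with the opportunity to give feedback".

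**The concern.** There are two gaps, both in the reasoning under Primary outcome.

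First, an expectation of less bias at 6 months helps the reader only if the arms are compared at 6 months. Followed as written, the plan produces no such comparison. A positive 3-month result would then stand without the later estimate that the section itself points to.

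Second, bias of equal size in both arms cancels in the between-arm difference, so only the differential part matters. Shared CR is a fair reason to expect the part tied to CR staff and setting to balance. It says nothing about a part tied to allocation. By design one arm has an extra 5 × 2 h = 10 hours of small-group contact with a nurse, with homework and feedback. If that contact leads patients to report more favourably, the 3-month difference is tilted towards CBT, and the remark about similar bias would carry into the interpretation unqualified.

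**Working it through.** **1. The plan's own figure.** Inputs from Sample size and power calculation: difference 2, SD 4, type 1 error 0.05, power 0.80. Statistical analysis adds that tests are two-sided.

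n per arm = 2 × (1.960 + 0.842)² × 4² / 2² = 62.8, so 63 by the normal approximation. The t-test version gives 63.8, so 64. The stated 64 reproduces, and this point disputes no number in the plan.

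**2. Is there a 6-month between-arm HADS contrast anywhere?**

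| Section | Use of 6-month HADS |
|---|---|
| Primary outcome | Remark that bias should be smaller then; endpoint set at 3 months |
| Table 1 | Collected |
| Secondary outcomes | Not listed |
| Sample size and power calculation | Re-evaluation of the 40 non-distressed patients |
| Statistical analysis, primary model | Covariate for the 3-month score |

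No section makes it an outcome of the randomized comparison.

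**3. What a differential bias would do (illustration).** The documents give no size for it, so the values of b are assumptions. Suppose no true effect and a differential of b points in favour of CBT:

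SE = 4 × √(2/64) = 0.707

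Rejection rate = Φ(b/SE − 1.960) + Φ(−b/SE − 1.960)

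| Assumed b (points) | Share of the 2-point target | Two-sided rejection rate |
|---|---|---|
| 0 | 0% | 5.0% |
| 0.25 | 12.5% | 6.4% |
| 0.5 | 25% | 10.9% |
| 1.0 | 50% | 29.3% |
| 1.5 | 75% | 56.4% |

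These figures describe a simple two-group comparison, not the planned adjusted model.

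**4. Does the planned use of the 6-month score act as a check?** No. The score is measured after randomization and can itself be affected by treatment. Assume equal variances, correlation ρ of baseline with each follow-up score, and correlation r between the 3- and 6-month scores. The coefficient on the 6-month score is then

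β₆ = (r − ρ²) / (1 − ρ²),

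and a true 3-month effect of 2 is estimated as 2 − β₆ × (6-month effect).

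- ρ = 0.5, r = 0.5, 6-month effect 2: β₆ = 0.25/0.75 = 0.333, giving 2 − 0.67 = 1.33.
- ρ = 0.7, r = 0.8, 6-month effect 2: β₆ = 0.31/0.51 = 0.608, giving 2 − 1.22 = 0.78.
- 6-month effect 0: the estimate stays at 2.

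Under these assumed correlations (0.5 to 0.8), a lasting 2-point effect would be reported as about 0.8 to 1.3 points. The covariate gives no information on persistence and can distort the primary estimate.

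**5. Power for a 6-month contrast.** If the SD of change at 6 months is also 4 (assumption), 64 per arm gives Φ(2/0.707 − 1.960) = Φ(0.868) = 0.81 for 2 points. No extra patients are needed.

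**The case against.** The strongest case on the other side has four parts.

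- **The plan's wording is cautious.** It says only that the arms may have similar bias, and that a reduction is anticipated. A reader might infer that the plan asserts equal bias and sets month 6 as a formal safeguard that is then never used. The text does not support that. Unsupervised completion is a safeguard in use, and the 6-month score is used, though only as a covariate. The primary analyses are also done without knowledge of allocation, although that cannot cure bias in self-report.
- **Differential bias is not shown.** A reader might infer that the bias does differ by arm. Extra contact in one arm makes this plausible, but nothing in the article establishes it or its size, and zero is not excluded. An assumed 0.25 points barely moves the error rate.
- **The article may be condensed.** Secondary outcomes such as return to work are also to be analysed by repeated measures regression, so a longitudinal HADS model may have been intended, and the analysis plan is not shown. This tempers the point. But the article does state the outcome list and the primary model, and the role it gives the 6-month score in that model is that of a covariate.
- **A 6-month estimate does not test the bias.** A fading difference could be fading bias or fading effect, and a persisting one could be persisting bias. This stands in full. A rule tying a claim of durable benefit to the 6-month result would be a preference, not a correction.

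One further inference is unsupported: that clinic staff see the answers because forms are handed back on site. The article says that "Questionnaire responses (all on paper) will be entered into electronic form in REDCap immediately after the assessment", but not how forms are returned or who enters them.

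**Conclusion.** The point holds in a limited form. The plan offers 6 months as the time of reduced reporting bias and collects HADS then, but as written it yields no between-arm result at that time. The remark on similar bias covers shared CR only, so the bias may differ by arm and may favour CBT.

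The size is unknown. The range of about 11% to 29% rests entirely on an assumed differential of 0.5 to 1.0 points, no true effect, SD 4 and 64 per arm. It shows sensitivity and is not evidence that bias is present. The attenuation to 0.8 to 1.3 points rests on assumed correlations and on a 6-month effect as large as the 3-month one.

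This is a free improvement: the data are already scheduled, and the gain is a result on persistence and a more accurate caveat.

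**What to change.** 1. Under Secondary outcomes, add the between-arm difference in HADS total score at 6 months.
2. Under Statistical analysis, estimate the 3- and 6-month differences from one repeated-measures model with both follow-up scores as responses, an arm-by-time term, centre, and baseline as the only HADS covariate. Remove the 6-month score as an adjustment variable for the 3-month outcome; adding the secondary outcome without this step would leave the primary estimate open to distortion.
3. Report the 6-month estimate and its confidence interval beside the 3-month result, and describe it as evidence on persistence, not as a test for bias.
4. Under Primary outcome, qualify the remark on similar bias: shared CR may balance bias tied to the common setting, but the added sessions are given to one arm only, so reporting bias may favour CBT.

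The cost is wording and a model specification. There are no extra patients, visits or questionnaires, and the 3-month difference remains the sole primary comparison. The one downside is a more cautious conclusion if the difference fades by 6 months.

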### Secondary outcomes

Secondary outcomes are adherence to CR defined as > 80% participation in planned training sessions (used as a secondary outcome under the hypothesis that participation in group-based therapy will improve CR adherence), health-related QoL measured by the questionnaire HeartQoL, return to work, marital status, adherence to medication and lifestyle interventions for CVD risk factor goals defined as four separate outcomes: HbA1c < 48, BP < 135/85 mmHg, BMI < 30 and LDL < 1.4 mmol/l, physical activity (days per week with ≥ 30 min of moderate physical activity) and cardiovascular readmissions at 12 months.

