**Clinical measurements**									
Weight	x						x	x	
Heart rate	x						x	x	
Blood pressure	x						x	x	
ECG	x						x	x	
Biochemical screening	x						x	x	
NYHA classification	x						x	x	
CCS classification	x						x	x	
**Medication**	x						x	x	

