### Sample size and power calculation

The primary outcome is a change in HADS score at 3 months. A clinically relevant difference between groups would be a reduction in the total sum score of 2. In a previous study [36], the change within each group was normally distributed with a standard deviation (SD) of 2.5. We have here used a more conservative estimate with an SD of 4. Under these assumptions with a risk of type 1 error of 0.05 and a power of 0.8, 64 patients should be included in each group. Due to the risk of dropout of patients included in this type of trial, the total number of patients included is increased by 15% to 148 patients

STATA II, the Ralloc programme is used for randomization, permuting random block sizes of 2,4 and 6.

To assess the spontaneous variation in HADS scores over time, we will investigate a non-randomized group of 40 matched patients (relative to inclusion and exclusion criteria) without signs of psychological distress (i.e. HADS A < 8 and HADS D < 8) at first measurement with re-evaluation after 3 and 6 months. With 64 patients in the usual care arm and assuming a SD of 4 as above, we will have 80% power to detect a difference in change in HADS score (delta HADS) of 2.3 or more between these two groups.

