### Statistical analysis

The primary analysis will be a comparison of the intervention and control group in mixed-models linear regression with robust standard errors with 3-month values as outcome, and baseline and 6 months values will be used as adjustment variables. Analyses will also be adjusted for the centre and tested for treatment-centre interaction. For the analysis of the secondary outcomes return to work (yes/no), HbA1c< 48, BP< 135/85 mmHg, BMI< 30, LDL< 1.4 mmol/l and physical activity, we will also apply repeated measures regression. For adherence to CR (> 80%), we will compare groups by logistic regression adjusting for the centre. For the outcome of re-admission at 12 months, we will compare outcomes across groups with Kaplan-Meier curves and time-to-event analyses (Cox regression) adjusting for age, left ventricular ejection fraction, co-morbidities and risk factors as described above. A two-sided P < 0.05 will be considered statistically significant, and all primary outcome analyses will be performed without knowledge of group allocation.

We will compare the primary outcome in intervention and control groups with the spontaneous variation in the non-distressed subgroup of 40 participants by separate mixed-models linear regression adjusting for baseline values and centre.

The primary reported analyses will be carried out as a modified intention-to-treat as participants with missing data on a primary or secondary outcome will be excluded from the corresponding analyses. The analysis is supplemented with per-protocol analyses defined by participation in ≥ 4 of the 5 group-based sessions. Missing information on other co-variates will be permuted if there is < 20% missing data for the co-variate in question.

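### The four risk-factor outcomes are specified only as goal met or not met; a supportive analysis of the measured HbA1c, BP, BMI and LDL values would be more precise and needs no new data

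*Protocol article*

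**What the plan says.** Under Secondary outcomes, the protocol article sets the risk-factor goals as thresholds, "HbA1c < 48, BP < 135/85 mmHg, BMI < 30 and LDL < 1.4 mmol/l". Under Statistical analysis the same thresholds reappear: for "HbA1c< 48, BP< 135/85 mmHg, BMI< 30, LDL< 1.4 mmol/l and physical activity, we will also apply repeated measures regression". No analysis of these four variables on their measured scale is stated. Physical activity, named in the same sentence, is kept as a number of days per week.

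Table 1 schedules weight, "Blood pressure" and "Biochemical screening" at baseline, 3 and 6 months. HbA1c and LDL are not named there. That they fall under the biochemical screening is an inference, as is deriving BMI from the scheduled weight.

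The significance rule is general: "A two-sided P < 0.05 will be considered statistically significant". The sample size rests on HADS alone: "a risk of type 1 error of 0.05 and a power of 0.8, 64 patients should be included in each group". No attainment rate, effect size or power is given for the risk-factor outcomes.

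**The concern.** Each goal is scored from a number, and the scoring keeps only which side of the line the number falls on. A patient whose LDL drops a long way but stays above the limit counts the same as one whose LDL does not move. The eligibility criteria do not require anyone to be above a limit at entry, so some patients will already be at goal and can show benefit only by staying there.

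The trial is sized for HADS, so the secondary outcomes have no planned reserve of power. If the goal comparisons show no difference, the reader cannot easily tell an absent effect from one blurred by the cut-point, although the values that would help separate the two should already be in the database.

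**Working it through.** **Inputs from the protocol article.** Two-sided alpha 0.05, power 0.80, difference 2, SD 4, 64 per arm, 15% inflation to 148 in total.

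**Inputs assumed here.** An approximately normal risk factor, a treatment effect that is a uniform shift, goal attainment p from 10% to 90%, and a shift of 0.5 SD. The shift is the standardised HADS effect (2/4), used only for illustration.

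**1. The plan's own figure.** n per arm = 2(1.960 + 0.842)² × 4²/2² = 62.8, or 63. The t-test version gives 63.8, or 64, as stated. Inflation: 64 × 1.15 = 73.6, or 74 per arm and 148 in total. Both figures reproduce.

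**2. Information kept by a yes/no comparison.** Relative to a comparison of means, the efficiency is φ(z_p)² / [p(1 − p)], where φ is the standard normal density and z_p the cut-point met by a proportion p. For p = 0.50: 0.3989²/0.25 = 0.637. For p = 0.80: 0.2800²/0.16 = 0.490. For p = 0.90: 0.1755²/0.09 = 0.342. The formula is symmetric, so 10% equals 90%.

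| Attainment | Efficiency | Loss |
|---|---|---|
| 50% | 0.64 | 36% |
| 30% or 70% | 0.58 | 42% |
| 20% or 80% | 0.49 | 51% |
| 10% or 90% | 0.34 | 66% |
| 5% or 95% | 0.22 | 78% |

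Under this model 36% is the smallest possible loss.

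**3. Power at 64 per arm, 0.5 SD shift.** Continuous: 0.5/√(2/64) = 2.828, and Φ(2.828 − 1.960) = 0.81. Yes/no: p₂ = Φ(z_p + 0.5), and power = Φ(|p₂ − p₁|/SE − 1.960), with SE = √{[p₁(1 − p₁) + p₂(1 − p₂)]/64}. Example at p₁ = 0.80: p₂ = 0.910, SE = 0.0615, ratio 0.1101/0.0615 = 1.79, power 0.43.

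| Control attainment | Intervention attainment | Power |
|---|---|---|
| 10% | 22% | 45% |
| 20% | 37% | 57% |
| 30% | 49% | 61% |
| 50% | 69% | 61% |
| 70% | 85% | 52% |
| 80% | 91% | 43% |
| 90% | 96% | 29% |

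A pooled variance lowers these by about one point. It gives 60%, 51%, 42% and 29% at 50%, 70%, 80% and 90%.

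**4. Smaller effect.** With a 0.2 SD shift, the continuous comparison has about 20% power and the yes/no comparison 9% to 15% across 50% to 90% attainment. Both are weak.

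**5. Baseline adjustment.** If each analysis adjusts for its own baseline (the value, or goal status), the efficiency in step 2 is multiplied by (1 − r²)/(1 − φ_b²). Here r is the baseline-to-follow-up correlation of the values and φ_b that of goal status. With an assumed r = 0.5, φ_b is 0.333, 0.295 and 0.251 at 50%, 80% and 90% attainment, and the loss is 46%, 60% and 73%.

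**Limits.** The BP goal joins two variables, so the one-variable formula is only approximate there. Step 3 is an unadjusted comparison at one time point, whereas the plan uses repeated measures.

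**The case against.** The strongest reply is that the threshold is the construct. The protocol asks whether patients reach risk-factor goals, and a mean LDL answers a different question. This stands: nothing in the document is contradicted or miscalculated, and replacing the goals with means would change the question asked.

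A second reply is that a journal article need not list every supportive analysis, and an unseen analysis plan may contain continuous ones. That is possible. The point is limited to what the article fixes, which is thresholds in both the definition and the analysis.

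Third, the size of the loss depends on an attainment rate and an effect the document does not give. This also stands, and it is why a range on both sides of 50% is shown.

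A reader might go further and infer that these outcomes are close to uninformative, or that patients at goal at baseline contribute nothing. Neither is supported. Under the same illustrative model the yes/no comparison keeps 43% to 61% power between 20% and 80% attainment. Patients at goal can lose it, and keeping it is part of adherence and counts in the comparison between arms. Nor would continuous analysis rescue these outcomes in every case: for a small effect, a trial of this size is weak on either scale.

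**Conclusion.** The point holds as a low-cost improvement to secondary outcomes, not as an error. The article specifies HbA1c, BP, BMI and LDL only as goal met or not met, while the values behind the goals must be obtained to score them.

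The cost in precision is at least about a third of the information and reaches about two thirds when 10% or 90% of patients meet the goal. It is larger beyond that range. These figures assume normality and a uniform shift, and the power figures also borrow 0.5 SD from HADS. The primary outcome and its sample size are unaffected.

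**What to change.** Keep attainment of each goal as the named secondary outcome, reported by arm with a confidence interval. Pre-specify alongside it a repeated measures analysis of the continuous values of HbA1c, systolic BP, diastolic BP, BMI and LDL, adjusted for the baseline value and centre, and label it supportive. Both BP components are needed because the stated goal has two parts. State also that HbA1c and LDL are taken at the scheduled biochemical screenings, if that is so.

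No new data, visits or patients are needed. The cost is five supportive analyses, which must not be presented as additional confirmatory tests, and a dated, justified change to the plan. The article reports that enrolment is still under way, so the change should be recorded before any results by arm are seen.
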